### 2.11. Statistical Analysis

Paired t-tests will be used to compare continuous baseline data with follow-up data for normally distributed variables, or Wilcoxon signed-rank tests for non-normally distributed variables. McNemar’s tests will be used to analyse categorical data. Multivariable logistic regression analysis with repeated measures will be conducted to assess dichotomous outcomes (e.g., ≥5% weight loss versus not), taking into account important covariates and paired data. Statistical significance will be demonstrated with a *p*-value of 0.05 and Cohen’s d will be used to indicate effect size. Analysis will be conducted for the complete cohort (intention-to-treat), as well as for those that complete the HAPIFED program. Median number of sessions, sociodemographic factors, outcomes, and scores will be compared between completers and noncompleters. Cost-effectiveness will be assessed using the quality of life data, health service utilization costs (determined from the self-report cost-effectiveness questionnaire and costed using the Medicare Benefits Schedule), and medication costs (using the Pharmaceutical Benefits Scheme), as previously published [77,78].

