### 2.2. Study Design

This will be a prospective study of the real-world effectiveness of the HAPIFED program for the treatment of individuals with overweight or obesity and who identify as having comorbid disordered binge eating behaviours that are characteristic of comorbid binge eating disorder, bulimia nervosa, or OSFED with recurrent binge eating.

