#### 2.6.1. Inclusion Criteria

Male or female aged 18 years and over;Able to read, write and communicate in English and be willing to provide written, informed consent;A BMI of ≥25 kg/m^2^. This criterion includes individuals with obesity (BMI ≥ 30 kg/m^2^), as well as those with a BMI in the overweight range (25–29.9 kg/m^2^). A BMI of ≥25 kg/m^2^ is associated with an increased risk of disease [34,35]. Weight loss offers numerous health benefits to such individuals [37,38,43,44,45,47,48,49,50,52,53,54,55] and may indeed serve as a preventative measure in ensuring that an individual’s weight trajectory does not increase from the overweight to the obese range, as is often seen in those with binge eating disorder [59]. Individuals with a BMI of ≥25 kg/m^2^ often want and seek to lose weight [9,24]. It is therefore appropriate to allow such individuals to enter the study if they wish;A global score on the EDE-Q that is greater than 1 standard deviation (1.25) above the Australian community norm of 1.52 (i.e., above 2.77) [60];Willing to undertake the HAPIFED program of up to 30 weeks (approximately 7 months) in duration involving behavioural weight loss therapy and CBT-E, and to attend sessions regularly (i.e., not miss more than 3 sessions over the course of the program);Have access to a computer, the Internet and an e-mail account and be willing to complete the online questionnaires up to 156 weeks (36 months) from study entry.

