### 2.8. Outcome Measures

#### 2.8.1. Primary Outcomes

The co-primary outcomes are as follows:(1)The proportion of participants that have lost ≥5% of their baseline body weight at 52 weeks (12 months) after program commencement.(2)The proportion of participants that have a global score on the EDE-Q that is less than 1 standard deviation (1.25) above the Australian community norm of 1.52 (i.e., below 2.77) [60] at 52 weeks (12 months) after program commencement.

Weight loss of ≥5% of body weight is considered clinically significant [69] and is associated with a reduction in the risk of noncommunicable diseases as well as with improvements in overall health and quality of life [43,70,71]. Indeed, the Australian Government’s Therapeutic Goods Administration uses this level as a threshold for evidence of weight loss efficacy for weight loss medications.

The EDE-Q is a widely used and validated self-report version of the diagnostic, interview-based Eating Disorder Examination [72]. This questionnaire will provide a comprehensive assessment of the range and severity of eating disorder psychopathology. The rationale for using the outcome measure of a global score on the EDE-Q that is less than 1 standard deviation above community norms is for the purpose of comparison with previous studies involving CBT-E [22,73,74]. A reduction in the global score on the EDE-Q to a value that is less than 1 standard deviation above community norms is considered a good outcome or ‘remission’ [22], and indeed, the majority of studies conducted with CBT-E used this threshold as a measure of efficacy [22,73,74].

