#### 2.8.2. Secondary Outcomes

The secondary outcomes are the change in the following parameters between baseline and follow-up at week 30 (approximately 7 months) and at 12, 24, and 36 months:Anthropometric parameters:○absolute weight;○weight as a percentage of baseline body weight;○BMI;○the proportion of participants who achieve ≥5% loss of baseline body weight;○the difference in the effect of HAPIFED on anthropometric parameters for people with different classifications of overweight or obesity at baseline (Overweight = BMI of 25–29.9 kg/m^2^; Class 1 Obesity = BMI of 30–34.9 kg/m^2^; Class 2 Obesity = BMI of 35–39.9 kg/m^2^; Class 3 Obesity = BMI of ≥40 kg/m^2^) [75]; Eating disorder parameters:
○severity of the eating disorder, as assessed using the EDE-Q [65,72]; Dietary parameters:
○nutritional quality of food choices, including the intake of fruit and vegetables, as assessed using the CSIRO Healthy Diet Score Survey [63]. The CSIRO Healthy Diet Score Survey is a scientifically validated survey that assesses an individual’s diet against Australia’s healthy eating guidelines [76]; Psychosocial parameters:
○depression, anxiety, and stress, as assessed using the DASS-21 [66]. The DASS-21 is a self-report scale with 21 items used to assess symptoms of depression, anxiety and stress;Quality of life as assessed using the SF-12v2 [67]. The SF-12v2 is a self-report scale with 12 items used to assess mental and physical functioning and overall health-related quality of life;Economic parameters:
○cost-effectiveness of the HAPIFED program as assessed by the use of a questionnaire to determine health-care utilization, medication use, and days off work.

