### 2.10. Sample Size

Based on the Australian government’s recommendation for obesity treatments that at least 50% of participants in a treatment group must achieve a weight loss of at least 5% of initial body weight to demonstrate a clinically significant benefit [69], and the HAPIFED pilot results where 50% of the sample had an EDE-Q score of less than one standard deviation (1.25) above the community normative score of 1.52 (i.e., below 2.77) [56,60] at the end of treatment (whereas all had a score above 2.77 before treatment), we estimated that a sample size of at least 164 participants (with 5% significance level and power of 80%) is required. To allow for an up to 50% attrition rate as that found in the pilot study [56], we inflated the sample size to 246 to ensure complete data. 

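### Both co-primary outcomes are 0% at baseline by construction, so a McNemar comparison of week 52 with baseline tests only whether the responder rate is zero

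*Protocol article*

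**What the plan says.** Section 2.2 describes one cohort and no comparison group: "This will be a prospective study of the real-world effectiveness of the HAPIFED program".

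Section 2.8.1 defines two co-primary outcomes, both proportions at week 52. The first is "The proportion of participants that have lost ≥5% of their baseline body weight at 52 weeks (12 months) after program commencement". The second is the proportion whose EDE-Q global score is "less than 1 standard deviation (1.25) above the Australian community norm of 1.52 (i.e., below 2.77".

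Section 2.6.1 admits only people with "A global score on the EDE-Q that is greater than 1 standard deviation (1.25) above the Australian community norm of 1.52 (i.e., above 2.77". Table 1 lists the EDE-Q once before treatment, in a combined screening/baseline column.

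Section 2.11 first assigns paired tests to the comparison of continuous baseline and follow-up data. It continues: "McNemar’s tests will be used to analyse categorical data. Multivariable logistic regression analysis with repeated measures will be conducted to assess dichotomous outcomes", with ≥5% weight loss as the example, and says that the regression takes account of covariates and paired data. The criterion for significance is a p-value of 0.05.

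Section 2.8.2 lists, among parameters whose change from baseline is of interest, "the proportion of participants who achieve ≥5% loss of baseline body weight".

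Section 2.10 cites a government recommendation that at least 50% of a treated group should lose at least 5% of initial weight. It also cites a pilot in which 50% were below the EDE-Q cut-off at the end of treatment. Neither figure reappears in section 2.11.

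**The concern.** McNemar's test compares the two kinds of change: participants who move from non-responder to responder, and those who move the other way. When nobody can be a responder at baseline, the second kind cannot occur. The null hypothesis of equal proportions then becomes a responder rate of zero, which a handful of responders is enough to reject.

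With no control group and no reference proportion in section 2.11, that p-value could become the study's headline. A programme in which one participant in twenty reached each outcome could be reported as significant on both co-primaries. The reader would learn nothing about whether the rate is near the 50% that section 2.10 treats as clinically meaningful.

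A related risk concerns the logistic model. If baseline is one of its repeated outcomes, every baseline value is zero and the effect of time has no finite estimate.

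**Working it through.** **Inputs.** The significance level and power come from section 2.10: "with 5% significance level and power of 80"%. Sidedness is not stated; two-sided is assumed. The denominators are 164 (the target before attrition in section 2.10) and 123, which is the inflated 246 after the 50% attrition quoted there (246 × 0.5).

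**Step 1: baseline rates.** Weight: loss relative to baseline is 0% at baseline, so no one is a responder. EDE-Q: success is a score below 2.77, entry requires a score above 2.77, and the same single assessment serves as screening and baseline. Both rates are exactly 0%.

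**Step 2: does the planned size come from this test?** For McNemar with 0% at baseline and 50% at week 52, the discordant proportions are 0.5 and 0. Then n = [1.960 × √0.5 + 0.842 × √(0.5 − 0.25)]² / 0.25 = 13.06, or 14 pairs; the exact test needs 15 (power 0.85; 14 gives 0.79). The plan's 164 is therefore not reproduced by this comparison. The basis of 164 is a separate question; here the result shows only how little the baseline comparison demands.

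**Step 3: responders needed for p < 0.05.** Let b be the number of week-52 responders; the opposite discordant cell is 0. The exact two-sided p is 2 × 0.5^b, the uncorrected chi-square is b, and the corrected chi-square is (b − 1)²/b.

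| b | Exact p | Corrected p | Uncorrected p |
|---|---|---|---|
| 3 | 0.25 | 0.248 | 0.083 |
| 4 | 0.125 | 0.134 | 0.0455 |
| 5 | 0.0625 | 0.074 | 0.025 |
| 6 | 0.031 | 0.041 | 0.014 |

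The threshold is 6 (exact or corrected) or 4 (uncorrected), whatever the sample size. Six is 6/164 = 3.7% or 6/123 = 4.9%. The matched odds ratio, b/0, is infinite.

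**Step 4: what that result would mean.** The Wilson 95% interval for 6/164 is 1.7% to 7.8%, and for 6/123 it is 2.3% to 10.2%. Both lie far below 50%, yet McNemar would be significant. As an illustration, suppose the true responder rate were 5%, a tenth of the benchmark. The binomial probability of at least 6 responders is 0.83 with 164 analysed and 0.58 with 123. The 5% is an assumed value.

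**Step 5: the logistic model.** In simulated data with an all-zero baseline visit, ordinary logistic time coefficients grew with the number of iterations (about 11, 21, then 37) while standard errors rose from 15 to 2,283 to about 5 million. That is the signature of separation. The same data restricted to the four follow-up visits converged normally, with time contrasts of about 0.4 and standard errors of about 0.2. The model fails only if baseline is included as an outcome.

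**The case against.** The strongest reply is that section 2.11 never names McNemar as the co-primary test. It states the baseline-to-follow-up contrast in words only for continuous data, gives McNemar to categorical data in general, and then gives dichotomous outcomes, with ≥5% weight loss as the example, to logistic regression. McNemar between two follow-up visits is sound. A condensed article may also leave the exact contrast to an analysis plan that is not shown.

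Part of this stands. The baseline pairing is inferred, though it is the natural one: the sentence follows directly on baseline comparisons, the cohort has no other comparator, and both outcomes belong to a single visit. The objection concerns a test that the article does name, which for these outcomes is uninformative in its natural use. A later plan would have to change that choice, not just add detail.

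Three stronger readings are tempting, and the documents do not support them.

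- A reader might infer that the repeated-measures regression is itself degenerate. Section 2.11 does not say that baseline is one of the repeated outcomes. The mention of paired data makes that possible without settling it, and a follow-up-only model is estimable.
- A reader might infer a false-positive rate from participants crossing the EDE-Q cut-off through measurement noise. The documents give no such crossing rate. Change without treatment is in any case a limit of the uncontrolled design rather than of McNemar.
- A reader might infer that success should require the lower confidence limit to exceed 50%. The recommendation in section 2.10 is that at least 50% achieve the loss, which is a different rule. An exact two-sided test against 50% would need 96/164 (58.5%) or 73/123 (59.3%), and the study was not planned around that.

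**Conclusion.** The point holds in conditional form. It is certain that both co-primaries are 0% at baseline. If McNemar is applied to them as baseline against week 52, it tests a zero responder rate and is significant at 6 responders (exact or corrected) or 4 (uncorrected), about 2% to 5% of the analysed cohort (4/164 = 2.4%; 6/123 = 4.9%). Such a result carries no information about the 50% figures in section 2.10. Section 2.11 supplies no other reference for the co-primaries, and a follow-up-only regression, though estimable, does not by itself compare the week-52 proportion with anything.

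This rests on a two-sided 5% level and on the natural pairing in a single cohort. The regression problem arises only if baseline is entered as a repeated outcome, which the text leaves open. McNemar remains valid between follow-up visits and for other categorical variables.

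**What to change.** - **Co-primaries:** make the week-52 proportion, with an exact or Wilson 95% confidence interval, the main result for each. Interpret weight against the 50% already cited in section 2.10. Interpret EDE-Q against the 50% pilot rate given there, or against a remission rate that the sponsor states before the data are seen. For scale, 82/164 would give a Wilson interval of 42.4% to 57.6%.
- **McNemar:** state that it will not be used against baseline for the co-primaries or for the secondary ≥5% weight-loss proportion in section 2.8.2. Keep it for comparisons between follow-up visits and for other categorical variables.
- **Logistic model:** state that the repeated outcomes are weeks 30, 52, 104 and 156 only, with baseline weight or BMI and baseline EDE-Q score as covariates.

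The cost is analysis wording; no new data or visits are needed. The downside for the sponsor is a less favourable presentation than a comparison with zero.

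### The tests named for the intention-to-treat analysis cannot include participants without follow-up values, and over-recruiting for up to 50% attrition does not remove the possible bias

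*Protocol article*

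**What the plan says.** Section 2.11 names two analysis populations: "Analysis will be conducted for the complete cohort (intention-to-treat), as well as for those that complete the HAPIFED program".

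For continuous outcomes it states: "Paired t-tests will be used to compare continuous baseline data with follow-up data for normally distributed variables", with the Wilcoxon signed-rank test where normality fails. For categorical outcomes: "McNemar’s tests will be used to analyse categorical data". It adds a model for binary outcomes: "Multivariable logistic regression analysis with repeated measures will be conducted to assess dichotomous outcomes (e.g., ≥5% weight loss versus not".

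Section 2.10 deals with attrition through numbers alone. It begins "To allow for an up to 50% attrition rate as that found in the pilot study" and ends "we inflated the sample size to 246 to ensure complete data".

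Section 2.8.1 defines both co-primary outcomes as proportions of participants at week 52. Under section 2.7.2, outcomes come from online questionnaires requested by e-mail, with at most two reminders at each time point. The article gives no rule for counting a participant whose week-52 weight or EDE-Q is missing.

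**The concern.** The population label and the named tests do not match. A paired test needs a pair, so a participant with no follow-up value cannot enter it unless a value is imputed. The sample-size text points the same way: inflating recruitment so that enough complete data remain makes sense if those lost are expected to leave the analysis. If every starter were counted, that inflation would not be needed for this purpose.

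More is at stake here than in a randomised comparison. The study has one group, so there is no comparator in which similar loss might partly cancel the bias. Any link between success and answering the week-52 questionnaire passes straight into the two headline proportions, and section 2.10 sets the weight result beside a 50% benchmark. The paired tests at week 52 also make no use of week-30 values from participants who are missing at week 52.

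**Working it through.** **Inputs from the article.** Base sample size 164, attrition up to 50% and recruitment target 246 (section 2.10). Named methods (section 2.11). Co-primaries as week-52 proportions (section 2.8.1).

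**Inputs assumed.** Success among respondents, p_r = 50%. Section 2.10 gives 50% as the weight benchmark and as the pilot EDE-Q result, not as a rate among respondents. Success among those lost, p_m, is not given and is varied from 0% to 50%.

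**Step 1: the plan's own figure.** 164 × (1 + 0.5) = 246, so the target is reproduced by multiplying by one plus the attrition rate. With the full 50% loss, 246 × (1 − 0.5) = 123 participants are observed. (Keeping 164 would need 164 / (1 − 0.5) = 328; 246 keeps 164 only at a loss of 82/246 = 33.3%. That is a separate sample-size matter and is not needed for this point.)

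**Step 2: who contributes to each named method at week 52, without imputation.**

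| Method | Has week-52 value | Has week-30 value only | No post-baseline value |
|---|---|---|---|
| Paired t / Wilcoxon signed-rank | yes | no | no |
| McNemar | yes | no | no |
| Repeated-measures logistic regression | yes | yes, through week 30 | no outcome |

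No row covers the complete cohort. The regression comes closest.

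**Step 3: effect on a co-primary proportion.** With attrition a:

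- whole-cohort rate = (1 − a) × p_r + a × p_m
- overstatement = p_r / whole-cohort rate

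At a = 50% and p_r = 50%:

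| p_m | Whole-cohort rate | Overstatement |
|---|---|---|
| 0% | 0.25 + 0 = 25% | 2.00 |
| 10% | 0.25 + 0.05 = 30% | 1.67 |
| 25% | 0.25 + 0.125 = 37.5% | 1.33 |
| 40% | 0.25 + 0.20 = 45% | 1.11 |
| 50% | 0.25 + 0.25 = 50% | 1.00 |

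At a = 1/3, p_m of 0%, 10%, 25% and 50% gives 33.3%, 36.7%, 41.7% and 50%, with ratios of 1.50, 1.36, 1.20 and 1.00. With p_m = 0 and smaller losses, the ratio is 1/(1 − a): 1.11 at 10% and 1.25 at 20%.

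The range of 1.0 to 2.0 supposes that those lost do no better than respondents. If they did better, respondents-only would understate: with p_m = 100% at a = 50%, the whole-cohort rate is 75%.

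**Step 4: counting missing as not achieved.** The rate then cannot exceed 1 − a. At 50% loss the ceiling is 50%, so the benchmark in section 2.10 ("at least 50% of participants in a treatment group must achieve a weight loss of at least 5% of initial body weight") is met only if every respondent succeeds. Whether the benchmark is met can therefore turn on a rule that the article does not state.

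**The case against.** Four points on the other side carry weight.

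- **The regression.** Both co-primaries are binary, and the example given for the repeated-measures logistic regression is the weight co-primary. That model can use week-30 data, so the loss of week-30 information is a fault of the paired tests and not of the whole plan. This stands. Participants with no post-baseline data remain outside it.
- **Silence is not a rule.** A reader might infer that the analysis labelled intention-to-treat is a complete-case analysis. The article nowhere says that participants without follow-up are dropped, paired tests can be run on imputed values, and a condensed article may leave the missing-data rule to a fuller document. This stands against stating complete-case analysis as fact. It does not remove the mismatch between the stated label and the stated tests, or the reliance on over-recruiting.
- **Attrition.** The figure is an upper allowance, and the article does not say whether the pilot loss was from the programme or from the questionnaires. Someone who leaves the programme can still answer at week 52, and section 2.11 plans to compare outcomes of completers and noncompleters. This stands: 50% missing at week 52 is a planning limit and not a forecast.
- **Direction.** A reader might take the remarks on disappointment and relapse (abstract and section 1) as showing that non-respondents to HAPIFED questionnaires are treatment failures. Those remarks concern treatments that address only one of the two conditions. They make informative loss plausible and do not establish it.

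**Conclusion.** The point holds in a limited form. The paired tests named in section 2.11 do not by themselves deliver the stated intention-to-treat analysis, the logistic regression narrows the gap without closing it, and the over-recruitment in section 2.10 addresses precision and not bias.

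The size is conditional. At the full 50% loss, with 50% success among respondents, a respondents-only proportion is too high by a factor between 1.0 (those lost succeed equally often) and 2.0 (none of them succeeds). A reader might take doubling as the expected result; it is the extreme case, and it falls to 1.5 at one-third loss even if nobody lost succeeds. The calculation rests on an assumed respondent rate, an assumed direction, and attrition that means missing week-52 outcomes. The documents do not support saying that the results will be biased, only that they could be, and that the stated methods give no protection for participants with no post-baseline data.

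**What to change.** **Continuous outcomes.** Replace the visit-by-visit paired tests with one likelihood-based mixed model for repeated measures over weeks 0, 30, 52, 104 and 156.

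**Co-primaries.** Define the denominator as all enrolled participants who start HAPIFED. Estimate the two week-52 proportions by multiple imputation using baseline and week-30 data. Report beside them (a) missing counted as not achieved, as a conservative bound, and (b) respondents only, as supportive. Counting missing as failure is better kept as a bound than made the sole primary rule, because at 50% loss it caps the rate at the plan's own benchmark.

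**Otherwise** drop the intention-to-treat label and describe the population as those with data at the visit. Either way, fix the rule before outcome data are seen.

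**Cost.** Changed analysis wording, modest programming, and probably a lower headline responder rate. The mixed model and the imputation assume that values are missing at random given the observed data. For participants with no post-baseline data, imputation rests on baseline alone, which is why the bound should be shown beside it.
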